### Music performance quality evaluated by anonymous experts

Upon termination of the experiments with all participants, the audio recordings will be sent to music experts for evaluation of the performances using the MPQ Scale. The experts will be professional musicians/teachers with a minimum requirement of master’s level training on their main performance instrument and with experience of professional assessment and adjudication (see [41–43] for similar criteria). They will have no association with the participants. We will have five judges per instrument type [44, 45]. In order to minimize the influence of nonmusical factors on the evaluations [46, 47], judges will receive the recordings in an individually randomized order, work independently and be unaware of the conditions under which performances were recorded and of any personal data about the participants.

### Measures of the online entry questionnaire

#### Sociodemographic data

The sociodemographic data include age, gender, mother tongue, French or English level (on a scale from 1 = Do not speak and do not understand English/French to 5 = Speak and understand perfectly English/French), and night shift work (yes/no).

#### Academic and music-related data

The academic and music-related data include the name of the school, the department, the current academic year, the main instrument, the time they started to play their main instrument, the second instrument, the average number of hours per day of music practice, the number of public solo and ensemble performances given during the past 12 months.

#### Health-related data

We will ask participants to list any known disease and any acute or chronic medication intake and to answer the questions assessing panic disorder and eating disorders from the Patient Health Questionnaire (for English version [48]; for French version [49]). Women will be also asked to indicate whether they are pregnant, lactating or using hormonal contraceptives. Women will also indicate the first day and the length of their last period as well as the duration of their menstrual cycle. Moreover, participants will have to indicate if they wear a pacemaker, smoke or take recreational drugs.

#### General MPA level

The general MPA level will be assessed with the state scale of the State-Trait Anxiety Inventory (STAI-S; for English version [50], for French version [51]), which consists of 20 items, e.g., “I am tense,” rated on a 4-point Likert scale (1 “not at all” to 4 “very much so”). The score ranges from 20 (no anxiety) to 80 (severe anxiety). Because anxiety depends on the performance setting [52], we will ask students to indicate how they generally feel when they perform solo. We [8, 21] and others [e.g., [53, 54, 55]] have used this instrument to assess the general MPA level. The internal consistency of this questionnaire is excellent (Cronbach’s alpha > .90 [8, 21]).

The Kenny Music Performance Anxiety Inventory-Revised (for English version [56], for French version [57]) will be used as a complementary measure to the STAI-S. This questionnaire consists of 40 items evaluating eight MPA-related dimensions (proximal somatic anxiety and worry about performance, worry/dread focused on self/other scrutiny, depression/hopelessness, parental empathy, memory, generational transmission of anxiety, anxious apprehension and biological vulnerability). Each item is rated on a 7-point Likert scale (0 “Strongly disagree” to 6 “Strongly Agree”). The score can vary from 0 (no anxiety) to 240 (severe anxiety). The psychometric properties of this questionnaire are good [58].

### Performance session measures

For the measures assessed during the two performance sessions, we distinguish between primary and secondary measures. Primary measures are relevant to the study hypotheses. Secondary measures are assessed and analyzed for exploratory purposes.

#### Cardiovascular measures

Cardiovascular measures will be recorded and analyzed following international guidelines [59–61]. The VU-AMS (Free University, Amsterdam, The Netherlands) will be used to obtain impedance cardiographic and electrocardiographic recordings by applying seven electrodes on specific positions of participants’ thorax and back. We will analyze the data with the VU-AMS Data, Analysis & Management Software (Free University, Amsterdam, The Netherlands). The Finometer (FMS Finapres Medical Systems, Amsterdam, The Netherlands) will be used to record blood pressure (BP) beat-to-beat by finger-cuff photoplethysmography. A finger cuff is wrapped around the middle phalanx of the middle finger of participants’ left hand. A hydrostatic height correction of the finger with respect to the heart level is active during the entire recording. The Finometer recordings will be analyzed with the Beatscope software (FMS Finapres Medical Systems, Amsterdam, The Netherlands). Beat-to-beat BP recording is a significant advancement from the more often used single BP readings. The finger cuff will not be used during the performance, as it would interfere with performing. The primary cardiovascular measure is the CTI defined as the sum of CO and reverse scored TPR [33]. HR, HRV, stroke volume, systolic BP, diastolic BP, mean arterial pressure, CO, TPR and PEP are secondary cardiovascular measures.

#### Respiratory measures

Respiratory inductive plethysmography (RIP) sensors of the BioRadio (Great Lakes NeuroTechnologies, OH, USA) will be used to measure breathing parameters. This system consists of a thoracic band and an abdominal band that provide thoracic and abdominal motion signals, respectively. The proportionality constant between the thoracic and abdominal motion signals is determined by the qualitative diagnostic calibration method [62]. The RIP bands will be volume-calibrated using a spirometer (Vernier Software & Technology, Beaverton, OR, USA) at the beginning of each recording. The BioRadio recordings will be analyzed with the Vivosense software (Vivonoetics, Newport Beach, CA, USA). P_et_CO_2_ will be recorded by means of a nasal cannula connected to a nondispersive infrared CO_2_ monitor (Capnostream 35, Medtronic, Switzerland). The nasal cannula will not be used during the performance, as it would interfere with performing. The primary respiratory measures are sigh rate, total respiratory variability and P_et_CO_2_. Secondary respiratory measures include means of inspiratory time, expiratory time, total breath duration, tidal volume and minute ventilation. An embedded motion sensor in the BioRadio will record triaxial acceleration and angular velocity to quantify movement, both of which could affect other physiological measures.

#### Salivary measures

Saliva samples will be obtained via a passive drooling method facilitated by polypropylene straws into low-bind polypropylene 2 mL cryovials (Salicap, IBL International, Hamburg, Germany). For each saliva sample, participants will be instructed to rinse their mouth with water, swallow the saliva currently in their mouth, accumulate new saliva for 2 min and then transfer all saliva into the tubes. Samples will be stored immediately after collection at − 20 °C and then shipped on dry ice to the Biochemical Laboratory of the Department of Clinical Psychology, University of Vienna headed by Prof. [name], where they will be assayed for free cortisol and DHEA using immunoassay kits and for sAA using enzyme kinetic assay kits. SC, sDHEA and sAA are primary measures.

#### Self-reported demands and resources

Self-reported demands will be assessed before the performance (Q2) with the question “How demanding do you expect this music performance to be?” and after the performance (Q3) with the question “How demanding was the music performance situation?”. Self-reported resources will be assessed before the performance (Q2) with the question “How able are you to cope with the demands of the music performance?” and after the performance (Q3) with the question “How able were you to cope with the demands of the music performance situation?”. The participants will answer using a 6-point Likert scale ranging from 1 “not at all” to 6 “extremely”. These questions are adapted from the cognitive appraisal ratio [63, 64]. The resources-demands differential is the primary measure obtained by subtracting the score of the first question from the score of the second question. The self-reported demands and self-reported resources analyzed separately are secondary measures.

#### State anxiety

Self-rated state anxiety is a primary measure assessed before and after each performance (Q3 to Q6) with the 6-item version of the STAI (STAI-6; example item: “I am tense”), which yields results that are comparable to those obtained using the full-form [65]. Each item is rated on 4-point Likert scale (1 “not at all” to 4 “very much so”) and a sum score of all items is computed. Higher scores indicate greater state anxiety.

#### Music performance quality

MPQ is a primary measure assessed after each performance (Q3) with the MPQ Scale (See Additional file 1). This scale is a revised version of a MPQ scale used in a previous study [21]. The scale consists of nine dimensions (“tempo”, “rhythm”, “intonation”, “tone”, “dynamics”, “articulation”, “musical understanding and interpretation”, “missing notes, wrong notes and unwritten breaks” and “global appreciation”) to be rated on a 21-point scale ranging from 1 (= lowest score) to 6 (= highest score), with 0.25-point intervals to replicate the grading system of French-speaking Swiss schools. A definition is given for each dimension together with the specific aspects to consider in scoring the dimension. As done previously [21], we will compute an average score of these dimensions with higher scores corresponding to better MPQ.

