**Methods:**

We will test 100 university music students reporting general MPA levels ranging from low to high. They will perform privately (i.e., without audience) and publicly (i.e., with an audience) on two separate days in counterbalanced order. During each performance session, we will record their cardiovascular and respiratory activity and collect saliva samples and self-reported measures. Measures of primary interest are self-reported anxiety, the resources-demands differential, the cardiovascular challenge-threat index, sigh rate, total respiratory variability, partial pressure of end-tidal carbon dioxide and the salivary biomarkers cortisol, dehydroepiandrosterone, and alpha-amylase. Both, the participants and anonymous experts will evaluate the performance quality from audio recordings.

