*Relationship between general MPA level and challenge-threat*. Higher general MPA level is associated with greater increase in threat from the private to the public performance: With increasing general MPA level, change scores (public minus private) of the cardiovascular CTI and the resources-demands differential (self-rated resources minus self-rated demands) decrease.*Relationship between general MPA level and MPQ.* Higher general MPA level is associated with greater decrease in self-rated and expert-rated MPQ from the private to the public performance: With increasing general MPA level, change scores (public minus private) of self-rated and expert-rated MPQ decrease.*The mediating role of challenge-threat.* The cardiovascular CTI and the resources-demands differential are significant mediators of the relationships between general MPA level and self-rated and expert-rated MPQ.*Relationship between general MPA level and state anxiety.* Higher general MPA level is associated with greater increase in state anxiety from the private to the public performance: With increasing general MPA level, change scores (public minus private) of state anxiety increase.*Relationship between general MPA level and respiration.* Higher general MPA level is associated with greater increase in sigh rate and total respiratory variability and greater decrease in P_et_CO_2_: With increasing general MPA level, change scores (public minus private) of sigh rate and total respiratory variability increase, whereas change scores of P_et_CO_2_ decrease.*Relationship between general MPA level and salivary measures of HPA axis activity and SAM axis activity.* Higher general MPA level is associated with greater increase in sC and greater decrease in sDHEA, anabolic balance and sAA: With increasing general MPA level, change scores (public minus private) of sC increase, whereas change scores of sDHEA, anabolic balance and sAA decrease.

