**Fig. 2 Fig2:**
[figure not shown]
Performance session procedure – (Q = Questionnaire; S = Salivary sample) The quiet sitting periods correspond to a period where the participants are sitting alone at a table and required to keep their hands on the table, keep their eyes open, stay quiet and still and not cross their legs. Q1 consists of questions assessing participants’ compliance with the behavioral instructions (food intake, etc.) Q2 includes the questionnaires CSAI-2R (cognitive anxiety, somatic anxiety, self-confidence), self-reported demands and resources, STAI-6 and SAMq. Q3 includes the questionnaires FSS-2, MPQ Scale, CSAI-2R (somatic anxiety), self-reported demands and resources, STAI-6 and SAMq. Q4 and Q5 include the questionnaires CSAI-2R (somatic anxiety), STAI-6 and SAMq. Q6 includes the questionnaires CSAI-2R (somatic anxiety), STAI-6, SAMq, Post-Music Performance Thoughts Questionnaire, a question about performance engagement and a question about practice time.

The day before each performance session, the participants will receive an electronic reminder in which they are asked to comply with the following requirements: no alcohol intake and no intense physical activity 24 h before the visit, no heavy meal 1h15min before the visit, no caffeine intake (including coffee, tea or chocolate) 1h15min before the visit, no cigarettes or any products containing nicotine 1 h before the visit, and no food intake 15 min before the visit. The email for the public performance session will also remind the participants of the audience composition.

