### Final online questionnaire

One week after completing the second performance session, participants will receive the recordings of their two performances via an e-mail containing a link to a final online questionnaire and a Dropbox link to two mp3 audio files named “Recording1” for the first performance session and “Recording2” for the second performance session. In the online questionnaire, participants will be asked to listen to these audio files in the same order and rate the MPQ using the MPQ Scale.

Finally, the participant will fill in questionnaires assessing their trait anxiety, social anxiety and depressive symptoms, all of which are potential confounding variables because they can affect the psychophysiological measures.

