### Sample size calculation

The sample size calculation refers to the first three sets of hypotheses, which we consider to be the critical ones. The power computations are based on a model by which the effect of general MPA level on MPQ follows two paths, direct and indirect. In the indirect path, MPA acts on the cardiovascular CTI, which acts on MPQ. The computations rely on the repeated simulations of such a model. First, we fix the distributional parameters of MPA. We obtained a mean (*M*) of 45 on the STAI-S scale and a standard deviation (*SD)* of 12 [8]. We assume that general MPA level influences deltaCTI, i.e., the difference in CTI between private and public performance sessions. To simulate realistic values for deltaCTI, we rely on [85] who reported a difference in the cardiovascular CTI between a “challenge” group and a “threat” group of 0.9. Thus, we assume *M* = 0.9 for deltaCTI. Moore et al. [85] used a two-group design, while we use a repeated-measures design. To estimate *SD* of deltaCTI, we rely on [8] who used a similar design as in the planned project. In their study, *M* and *SD* of deltaHR between private and public sessions were 28 and 16, respectively. Assuming similar coefficients of variation for deltaHR and deltaCTI, we obtain *SD* = 0.9*16/28 = 0.5 for deltaCTI. From knowledge about distributions of general MPA level and deltaCTI and assuming normal distributions and linear relationships, we can deduce the equation of the linear regression from the following variance components: Var(deltaCTI) = variance of deltaCTI, Var_Res_ = residual variance, Var(MPA) = variance of MPA. The slope beta_deltaCTI_MPA_ is the square root of (Var(deltaCTI) – Var_Res_)/Var(MPA), and the intercept is mean(deltaCTI) - beta_deltaCTI_MPA_*mean(MPA). Defining the effect size using Cohen’s [86] η^2^, where η^2^ = (Var(deltaCTI)-VarRes)/ Var(deltaCTI), the model relating MPA and deltaCTI is specified. Next, we specify the effect of deltaCTI on deltaMPQ, where deltaMPQ is the difference in MPQ between public and private performance sessions. We assume a linear relationship with slope beta_deltaMPQ_deltaCTI_. Without any loss of generality, we can specify the linear relation without intercept and with residual *SD* = 1. Thus, the indirect effect of MPA on deltaMPQ is beta_indir_ = beta_deltaCTI_MPA_*beta_deltaMPQ_deltaCTI._ Next, we assume that there is also a direct effect given by the slope beta_dir_, which is determined by the assumed mediated proportion (MP): beta_dir_ = beta_deltaCTI_MPA_*beta_deltaMPQ_deltaCTI_*(1-MP)/MP. In summary, given a simulation of MPA, we simulate deltaCTI and deltaMPQ = beta_deltaMPQ_deltaCTI_ *deltaCTI + beta_dir_*MPA + e, e ~ N(0,1). Finally, we define that small-to-medium effects (according to [86] criteria for interpreting η^2^) of MPA on deltaMPQ, MPA on deltaCTI and deltaCTI on deltaMPQ and MP between 20 and 30% are scientifically meaningful. By running 10′000 simulations of the aforementioned model with different combinations of the parameters, we determine that these effects are significant at α = 0.05 and power > 0.80 with a sample of 100 participants.

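### Participants rate each performance twice on the MPQ Scale, the article does not settle which rating is the self-rated MPQ of hypothesis sets 2 and 3, and the audio rating is needlessly unmasked

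*Protocol article*

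**What the plan says.** All references are to the protocol article.

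- **Music performance quality** (performance session measures): "MPQ is a primary measure assessed after each performance (Q3) with the MPQ Scale". The legend of Fig. 2 agrees: "Q3 includes the questionnaires FSS-2, MPQ Scale, CSAI-2R (somatic anxiety), self-reported demands and resources, STAI-6 and SAMq".
- **Abstract, Methods**: "Both, the participants and anonymous experts will evaluate the performance quality from audio recordings". The abstract does not mention the rating given directly after playing.
- **Final online questionnaire**: one week after the second session, participants receive two files named by session number (Recording1, Recording2), and "participants will be asked to listen to these audio files in the same order and rate the MPQ using the MPQ Scale".
- **Background, hypotheses**: set 2 predicts that, with rising general MPA level, "change scores (public minus private) of self-rated and expert-rated MPQ decrease". Set 3 treats the CTI and the resources-demands differential as "significant mediators of the relationships between general MPA level and self-rated and expert-rated MPQ". Neither set says which self-rating is meant.
- **Sample size calculation**: "The sample size calculation refers to the first three sets of hypotheses, which we consider to be the critical ones".
- **Performance session measures** (opening paragraph): the split into primary and secondary is made for measures taken during the two performance sessions.
- **Music performance quality evaluated by anonymous experts**: experts receive the recordings in an individually randomised order and do not know the condition.
- **Data-analytic strategy**: alpha is 0.05 for every test.

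**The concern.** Two issues arise, and they are separate.

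The first is definition. Every participant produces two self-ratings per performance on the same instrument. One is given from memory immediately after playing. The other comes at least a week later, after listening to both performances one after the other. These need not give the same public-minus-private change. If the choice between them stays open, the self-rated test in set 2 and the self-rated half of set 3 each have two candidate outcomes.

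The second is masking. Participants learn their session order at the habituation session and then play both sessions, so file names and a listening order that follow the sessions tell them which recording was public. If high-MPA participants expect to have played worse in public, that expectation alone could produce the predicted relation between MPA and the change in the audio rating. The plan guards against knowledge of condition for the experts but takes no such step for the participants.

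**Working it through.** **1. Which hypotheses are touched.** Set 1 concerns "change scores (public minus private) of the cardiovascular CTI and the resources-demands differential", so MPQ plays no part in it. Set 2 has two MPQ outcomes, self-rated and expert-rated; one of the two is affected. Set 3 has 2 mediators × 2 outcomes = 4 mediation tests; the 2 with a self-rated outcome are affected. Self-rated MPQ is therefore an outcome in two of the three critical sets.

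**2. The two ratings side by side.**

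| | Rating at Q3 | Rating from recordings |
|---|---|---|
| Where described | Music performance quality; Fig. 2 legend | Abstract; Final online questionnaire |
| Scale | MPQ Scale | MPQ Scale |
| Timing | directly after each performance | requested 7 days after session 2, hence 7 + 2 = 9 days after session 1 |
| Stated status | primary | none |
| Condition known to the rater | yes, unavoidably | yes, by session-ordered names and listening order |

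The Q3 sentence speaks of MPQ in general, not of self-rated MPQ. Taken literally it would also place the expert ratings at Q3, although the experts rate only after all experiments have ended. It therefore cannot be the full definition of the MPQ outcomes.

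**3. What an open choice would cost.** Inputs: two two-sided tests at 0.05 (alpha from the Data-analytic strategy), critical value 1.96, and a correlation r between the two test statistics under the null. The article gives no r, so a range is assumed.

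P(at least one significant) = 1 − P(|Z1| < 1.96 and |Z2| < 1.96), with Z1 and Z2 bivariate normal.

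At r = 0 this is 1 − 0.95² = 0.0975. For support in the hypothesised direction only, P = 1 − P(Z1 < 1.96 and Z2 < 1.96), taking the predicted direction as positive. At r = 0 this is 1 − 0.975² = 0.0494.

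| Assumed r | Either test significant, any direction | In the hypothesised direction |
|---|---|---|
| 0 | 0.0975 | 0.0494 |
| 0.3 | 0.0951 | 0.0476 |
| 0.5 | 0.0907 | 0.0454 |
| 0.7 | 0.0835 | 0.0417 |
| 0.8 | 0.0781 | 0.0390 |
| 0.9 | 0.0704 | 0.0352 |

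With one named rating the two columns would read 0.05 and 0.025.

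**4. Listening order against knowledge of condition.** Participants are randomly assigned to private-first or public-first. Hearing the files in session order therefore does not favour public or private on average, and does not by itself bias the contrast or its relation to MPA. What remains is that the rater knows the condition. The documents give nothing from which to size the resulting bias.

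**5. Sample size.** The calculation does not depend on which self-rating is used, so N = 100 is untouched by this point.

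**The case against.** The strongest defence is that the body of the article largely settles the matter. The primary/secondary split covers session measures only; MPQ at Q3 is a session measure and is called primary; the audio rating is not a session measure and is nowhere called primary. The abstract's sentence is true as far as it goes and does not claim that the audio rating is primary or the only one. This stands to a large extent. A reader might infer that the article gives two incompatible primary definitions, and the documents do not support that: one rating is called primary and the other is left without a status. But the abstract names only the unclassified rating, and the hypotheses do not say which one they use, so Q3 is indicated rather than fixed.

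A reader might also infer that the false-positive rate of these tests is in fact inflated. Nothing in the article says that either rating may carry the claim. The figures are conditional on that and on an assumed correlation, and since set 2 is directional, the directional column is the fairer one for false support. Reporting both ratings together would also remove the selection concern.

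On masking, the expectation effect applies at least as much to the Q3 rating, where the participant has just played with or without an audience. It is therefore no reason to think the audio rating worse than Q3. Self-rated quality is also a perception, and part of what MPA does to it may belong to the construct; the masked expert ratings are the plan's safeguard. All of this stands. It leaves only the narrower observation that the audio rating could be partly masked at little cost, whereas Q3 cannot be.

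**Conclusion.** The point holds as a clarification worth making on a critical outcome, together with an inexpensive improvement to the audio rating. Two self-ratings exist, the article leans towards Q3 without settling it, and the abstract mentions only the other one. If the choice were left open, the false-positive rate of the affected test would be about 7% to 9.75% (3.5% to 4.9% in the hypothesised direction) instead of 5% (2.5%), for assumed correlations of 0.9 down to 0. With one rating named, the excess disappears.

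The audio rating is unmasked because file names and listening order follow the sessions. A reader might take the fixed order itself to be a source of bias; random assignment of session order rules that out for the public-private contrast. The issue is knowledge of condition. It is shared with Q3, cannot be removed there, and cannot be sized from the documents. Neither part affects the sample size.

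**What to change.** 1. State that the Q3 rating is the self-rated MPQ of hypothesis sets 2 and 3, which is the choice closest to the existing text.
2. State that the recording-based self-rating is secondary.
3. Align the abstract so that it mentions the rating given after each performance as well as the one from recordings.
4. Give each participant's two files neutral, randomly assigned labels and a random listening order, with the key held by the study team. The audio rating then serves as a partly masked check on the unavoidably open Q3 result.

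Cost: a few sentences and one file-naming step per participant, with no change to N, visits or instruments. Masking will be incomplete, because participants may recognise their own performances.
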